### Study endpoints

Our primary endpoint is the effect of spironolactone therapy on the change in placebo-corrected 6-minute walk distance at 24 weeks relative to baseline values and the incidence of clinical worsening in the spironolactone group compared to placebo. Clinical worsening will be defined as the addition of a new PAH-specific medication (a prostacyclin, an endothelin-1 receptor antagonist or a phosphodiesterase-5 inhibitor), dose or route escalation (that is inhaled prostacyclin changed to intravenous prostacyclin) of a current PAH-specific medication, development of right heart failure requiring hospitalization or an escalation in outpatient diuretic therapy (that is, initiation of a new diuretic or a dose escalation of current diuretic therapy), transplantation, or death.

Secondary endpoints include effect of spironolactone therapy on exercise capacity, as measured by the change in placebo-corrected VO_2_ maximum at 24 weeks relative to baseline values; effect of spironolactone therapy on plasma markers of vascular inflammation (see Table 2) and peripheral blood mononuclear cell (PBMC) gene expression profiles, comparing changes from baseline between the treatment and placebo groups; effect of spironolactone therapy on sympathetic nervous system activation, renin-angiotensin-aldosterone system activation and sex hormone metabolism, comparing changes from baseline between the treatment and control groups (see Table 2); effect of spironolactone therapy on RV function as assessed by echocardiography, magnetic resonance imaging (MRI) and N-terminal pro-brain natriuretic peptide (NT-proBNP), comparing changes from baseline between the treatment and placebo groups; and safety and tolerability of spironolactone therapy as determined by the rate of study drug discontinuation due to hyperkalemia (serum potassium ≥5.3 mEq/L), renal insufficiency (serum creatinine rise >50% of baseline), or other side effects such as breast pain and gynecomastia compared to placebo.

**Table 2 T2:** Biomarker assessment

**Markers of endothelial dysfunction**	**Neurohormonal axis**
**Adhesion molecules**	**Sympathetic activation**
sICAM-1, sVCAM-1, sE-selectin	Epinephrine, norepinephrine, arginine vasopressin
**Markers of activated coagulation**	**Renin-angiotensin-aldosterone system activation**
von Willebrand factor, thrombomodulin, sP-selectin	Renin activity, aldosterone, angiotensin II, NT-proBNP
**Cytokines and chemokines**	**Sex hormone metabolism**

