### Statistical considerations and analysis of the study

#### Sample size

Previous studies have examined the effects of PAH-specific therapy on time to clinical worsening, exercise capacity and endothelial inflammation in patients with PAH [59-63]. Moreover, the effects of spironolactone on endothelial dysfunction have been examined in diverse non-PAH patient populations [19-23]. However, no prior randomized controlled trials have been completed that report on the effects of spironolactone treatment in patients with PAH. Assuming that a subset of the participants with PAH may discontinue study drug or otherwise not be able to complete the study, we plan to enroll up to 70 participants with PAH to obtain at least 50 completed studies. The participants will be randomized in a 1:1 ratio to spironolactone therapy or placebo. At a two-sided α level of 0.05, we will have at least 84% power to detect an effect size (group mean difference divided by standard deviation) of 0.9 for the difference in the change of 6-minute walk distance from baseline between the two treatment groups [61].

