For secondary endpoints, LMMs will be used to assess the effect of spironolactone therapy on changes in VO_2_ maximum (24 weeks versus baseline), plasma markers of endothelial inflammation, sex hormone levels, and on activation of the renin-angiotensin-aldosterone and sympathetic nervous systems, as well as RV function as assessed by echocardiography, MRI and NT-proBNP. Random participant effect will be included to account for repeated measures within each participant over time. Transformations (for example, log-transformation) will be considered to stabilize variance. Standard residual diagnostics will be used to assess model assumption. VO_2_ maximum data may not be available for all participants. Based on the recent experience of the NHLBI pulmonary function laboratory at the NIH Clinical Center, approximately 5% to 10% of research participants have been unable to complete cardiopulmonary exercise testing or had incomplete data. We will collect information about the reason for missing VO_2_ maximum data. If the missing data can be considered ‘missing at random’ (for example, due to personal preference, orthopedic issues, inability to tolerate the mouthpiece or facemask), LMM is appropriate. For potentially informative missing data (for example, a participant is too sick to complete the procedure), to be conservative, a minimum value will be used for participants in the spironolactone group, and a last-observation-carry-forward approach will be used in the control group. The proportions of participants in the two treatment groups that have no VO_2_ maximum data will also be compared.

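### VO2 max that is missing because a participant is too sick is scored by treatment arm (a minimum on spironolactone, last observation on control), which biases this secondary endpoint against the drug

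*Protocol article*

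**What the plan says.** Study endpoints lists exercise capacity as a secondary endpoint, "as measured by the change in placebo-corrected VO_2_ maximum at 24 weeks relative to baseline values". Study analysis assigns it to a linear mixed model and expects incomplete data: "approximately 5% to 10% of research participants have been unable to complete cardiopulmonary exercise testing or had incomplete data". Missing values are then split by reason. Those that can be regarded as missing at random (personal preference, orthopedic problems, intolerance of the mouthpiece or mask) stay in the mixed model, with both arms treated alike. For the rest the text reads "For potentially informative missing data (for example, a participant is too sick to complete the procedure), to be conservative", followed by the rule "a minimum value will be used for participants in the spironolactone group, and a last-observation-carry-forward approach will be used in the control group".

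This is given as the handling of these data. It is not called a sensitivity analysis, and no symmetric alternative is named. One companion analysis is planned: "The proportions of participants in the two treatment groups that have no VO_2_ maximum data will also be compared".

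**The concern.** Being too sick to exercise is the same event in either arm. Under this rule it counts as a very poor result on spironolactone and as no further change since the last test on control. A gap between the arms is therefore built in even when the drug does nothing and equal numbers are too sick.

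The control half of the rule adds to the gap. Individual participant stopping rules describes the disease as progressive, yet carrying the last value forward hides the decline of control participants who have become too ill to be tested.

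At stake are the estimate and interval for the effect on VO2 max. In a trial that describes itself as a pilot, those matter more than the test alone. Power to see a real benefit falls, and false signals of harm become more frequent than the nominal rate.

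**Working it through.** The article states no sample size, power or variability for VO2 max, so there is no figure of its own to reproduce.

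**Inputs from the article**
- The imputation rule by arm, and the 5% to 10% of tests not completed or incomplete for any reason (Study analysis).
- The plan in Sample size: "we plan to enroll up to 70 participants with PAH to obtain at least 50 completed studies", and "The participants will be randomized in a 1:1 ratio to spironolactone therapy or placebo". This gives 70/2 = 35 per arm at most and 50/2 = 25 per arm as the completer target.

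**Assumed inputs**
- VO2 max mean 14, baseline SD 3 to 4, change SD 2 mL/kg/min.
- An informative-missing share m that is equal in both arms.
- A two-sided 5% t-test on change, standing in for the mixed model.
- The minimum taken as the lowest observed value.

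**Step 1: direction.** With no drug effect,

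bias = -m × (mean carried-forward value - imputed minimum).

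This is negative whenever the minimum lies below the carried-forward values. For gaps of 3, 5 and 8 mL/kg/min:
- m = 0.02: -0.06, -0.10, -0.16
- m = 0.05: -0.15, -0.25, -0.40
- m = 0.10: -0.30, -0.50, -0.80

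**Step 2: simulation under no drug effect.**

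| Informative missing per arm | Bias (mL/kg/min) | False harm, 25 per arm | False harm, 35 per arm |
|---|---|---|---|
| 2% | about -0.2 | about 3% to 4% | about 4% |
| 5% | about -0.45 | about 7% | about 9% |
| 10% | about -0.9 | about 14% | about 22% |

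The nominal rate in that tail is 2.5%. The bias agrees with Step 1 at a gap of about 9 mL/kg/min (0.45/0.05 = 9; 0.9/0.10 = 9).

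**Step 3: a second set of assumptions.** Here there are 25 per arm, SD 3 to 5, within-person correlation 0.8, and missingness linked to decline.

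| Informative missing per arm | Bias (mL/kg/min) | Two-sided rejection | Rejection in favour of drug |
|---|---|---|---|
| 2.5% | -0.17 to -0.22 | 5.0% to 5.3% | 1.4% to 1.9% |
| 5% | -0.33 to -0.43 | 6.1% to 6.4% | 0.9% to 1.1% |
| 10% | -0.63 to -0.85 | 9.6% to 10.8% | 0.4% to 0.5% |

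The sign is the same and the error rates are milder. Rejections in favour of the drug fall below the nominal 2.5%.

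**Step 4: the same rule in both arms.** With the minimum in both arms, or last observation in both, the bias lies between -0.03 and +0.01 mL/kg/min. Two-sided rejection is 4.5% to 5.2%, with about 2.2% to 2.7% in favour of the drug.

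**Step 5: the undefined term.** If the minimum is the participant's own lowest earlier value, the bias is at most about -0.06 mL/kg/min. It is zero when only a baseline value exists, because the two rules then coincide.

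**The case against.** The asymmetry is deliberate, disclosed and labelled conservative. It makes a false claim of benefit less likely. It affects one secondary endpoint in a pilot and leaves the walk-distance and clinical-worsening analyses untouched. All of that stands, and it limits the severity.

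The size is also easily overstated. The 5% to 10% covers every cause, including those sent to the mixed model, so 10% informative missingness is a ceiling on that figure. At 25 per arm, 10% is only 2.5 participants per arm. If those who miss the test already had low values, the gap to the minimum narrows and the bias at 10% falls to about -0.5 to -0.65 mL/kg/min. The article does not say whether participants removed from the protocol for clinical deterioration also fall under the rule; they are not counted here.

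A reader might infer more than the article supports:
- **That an ineffective drug will look harmful.** Even in the worst case shown (10%, 35 per arm), about 78% of null trials show no significant harm.
- **That the rule breaks the blind because it needs the treatment code.** Imputation can follow unblinding, and nothing in the article says otherwise.
- **That exercise capacity is left without any usable evidence.** The comparison of proportions with no VO2 max data is symmetric and remains informative.

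The objection does not rescue the rule as the main handling. Conservatism here guards only against false benefit, while the stated aim is to estimate an effect.

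**Conclusion.** The point holds at moderate severity. As written, the rule biases the VO2 max estimate and its interval against spironolactone whenever informative missing values occur and the imputed minimum lies below the carried-forward values. That direction is algebraic.

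The size rests on assumed VO2 max values, on reading the minimum as the lowest observed value, and on how much of the 5% to 10% is informative. At 2% the error rate is close to nominal; at 5% the excess is modest; the 10% results should be read as an upper limit. On the own-minimum reading the problem almost disappears. That one undefined phrase can move the result from negligible to material is itself a reason to amend the text. The primary endpoints are unaffected, and the rule does not raise the risk of a false efficacy claim.

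**What to change.** Replace the arm-specific sentence in Study analysis, before unblinding, as follows:
- Apply one rule by reason for missingness to both arms. For participants too sick to complete the test, assign a shared worst rank across the pooled arms and compare by a rank-based test. A single pooled minimum is a simpler alternative. The minimum must not be taken separately within each arm, because the rule would then depend on allocation again.
- Define the minimum wherever the term is kept.
- Retain the present asymmetric rule only as a labelled worst-case sensitivity analysis.

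The worst-rank form avoids treating an imputed number as a real measurement, but it does not give a mean difference in mL/kg/min. The pooled minimum keeps that scale but treats single imputed values as observed. The cost is a sentence or two of text, since reasons for missing tests are already to be collected. The main result also loses its built-in margin against a false claim of benefit, which the sensitivity analysis would then supply.

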#### Microarray analysis

Samples and their corresponding results will be subjected to strict quality control standards to assure that specimens are processed in balanced batches, to minimize the lot and reagent batch effects. Raw data will be background corrected, transformed, quantile normalized and summarized using the robust multi-array average technique. A principal components analysis will be computed to assist with recognizing outlying microarrays, which, along with other quality control indicators, may lead to rejection or re-analysis of some samples. LMM will be used to compare the PBMC gene expression profiles between the two treatment groups at each time point after accounting for repeated measures of each patient. Gene selection will be based on calculated false discovery rate to control the number of false positive findings.

Significant genes from these analyses will be annotated using automated tools, and a literature search will be performed for relevant information relating to the set of significant results. Significantly over-represented terms from formal ontologies, such as GeneOntology using the Database for Annotation, Visualization and Integrated Discovery, will be reported. Additional bioinformatics tools such as, Ingenuity^®^ Pathway Analysis (Ingenuity^®^ Systems) will be used in the annotation step.

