#### Gene expression profiling of peripheral blood mononuclear cells using Affymetrix GeneChip^®^ Microarrays

PBMCs have repeated contact with the altered endothelial cell surface in PAH and therefore may harbor unique signatures that are indicative of the disease process [52-54]. In a recent pilot study comparing PBMC expression profiles from 10 patients with PAH with 10 age-, gender- and race-matched controls, we identified 321 differentially regulated genes at a 20% false discovery rate. Ingenuity^®^ Pathway Analysis (Ingenuity^®^ Systems, Redwood, CA, USA) identified gene signatures for inflammation, cell-to-cell signaling and interaction, cytoskeletal rearrangement, cellular movement, hemostasis, and cell death [55]. To determine the effects of spironolactone therapy on PBMC gene expression in patients with PAH, we will compare changes in expression profiles at 12 and 24 weeks from baseline (obtained under our Natural History Study) between the treatment and placebo groups.

Blood specimens will be encoded to ensure patient confidentiality. No gene expression information with patient identifiers will be placed in the medical chart or in public records. Total RNA will be isolated, precipitated and quantified. Once total RNA is prepared, samples can be safely stored for an additional year. If longer storage of RNA samples is necessary, a commercially available methodology can be used to safely store total RNA at −80°C for up to 10 years. Total RNA isolated from the patient’s PBMCs will be hybridized to Affymetrix GeneChip^®^ Human Gene 2.0 ST Arrays (Affymetrix^®^, Santa Clara, CA, USA). Expression profile results will be used to direct confirmatory testing using quantitative real-time polymerase chain reaction (PCR).

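### The microarray model compares arms visit by visit, while the PBMC expression endpoint is change from baseline; the stated contrast should be aligned and should use the baseline array

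*Protocol article*

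**What the plan says.** Three places in the protocol article describe the PBMC comparison.

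- **Study endpoints** lists among the secondary endpoints "peripheral blood mononuclear cell (PBMC) gene expression profiles, comparing changes from baseline between the treatment and placebo groups".
- **Gene expression profiling of peripheral blood mononuclear cells** repeats this with the visits named: "we will compare changes in expression profiles at 12 and 24 weeks from baseline". The baseline sample comes from the Natural History Study.
- **Microarray analysis**, the only section that states the PBMC model, says the linear mixed model will "compare the PBMC gene expression profiles between the two treatment groups at each time point after accounting for repeated measures of each patient". It mentions neither change nor baseline. On multiplicity it says "Gene selection will be based on calculated false discovery rate to control the number of false positive findings".

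For the other secondary endpoints, Study analysis also uses linear mixed models: "Random participant effect will be included to account for repeated measures within each participant over time".

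**The concern.** Two of the three places name a difference in change, and the one that states the model names a difference in level. An analyst could follow either and be faithful to some part of the protocol. With about 25 completers per arm, the two contrasts will rank genes differently whenever the arms happen to differ at baseline, so two gene lists could each claim support from the text.

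The reference to repeated measures does not settle the matter. If the model has a free mean for every arm and visit and is read off at each visit, the baseline rows add nothing to the week-12 and week-24 contrasts when data are complete. Baseline helps only if it enters as a covariate, if the arms share a baseline mean, or, at high enough correlation, if change is contrasted. Microarray analysis states none of these. Taken literally, its wording could even include a comparison of arms at baseline, which cannot show a drug effect.

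At stake are the power of the gene screen and the stability of its list. The validity of the test is not at stake.

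**Working it through.** **No figure to reproduce.** The document gives no power, standard deviation or correlation for the microarray comparison. Its only power statement concerns 6-minute walk distance and does not bear on this point.

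**Inputs.** From Sample size: 1:1 allocation and at least 50 completed studies, so n = 25 per arm. Assumed: equal variance σ² at baseline and follow-up, complete data, and correlation ρ between baseline and follow-up. Since ρ is not documented, a range is shown.

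**Variance of the arm contrast at one follow-up visit**

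- Level at that visit (also an arm-by-visit model with free means, complete data): 2σ²/n. With σ = 1 this is 2/25 = 0.08.
- Change score: (2σ²/n) × 2(1 − ρ).
- Baseline-adjusted, by covariate or common baseline mean: (2σ²/n) × (1 − ρ²), in large samples.

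**Variance relative to the level contrast**

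| ρ (assumed) | Level | Change, 2(1 − ρ) | Baseline-adjusted, 1 − ρ² |
|---|---|---|---|
| 0.3 | 1.00 | 1.40 | 0.91 |
| 0.5 | 1.00 | 1.00 | 0.75 |
| 0.7 | 1.00 | 0.60 | 0.51 |
| 0.8 | 1.00 | 0.40 | 0.36 |

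The change score beats the level contrast only when 2(1 − ρ) < 1, that is, when ρ > 0.5. The baseline-adjusted ratio never exceeds 1.

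**Simulation check.** This used 4,000 trials at each of ρ = 0.3, 0.5 and 0.7, with 25 per arm, equal baseline expectation and a true effect of 0.5 SD. The mean estimate was 0.49 to 0.51 for all three contrasts. Variance ratios were 1.36, 0.98 and 0.60 for change, and 0.90, 0.74 and 0.51 for the model with a common baseline mean, in line with the formulas.

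**Illustrative power** for one gene, with an assumed difference of 0.8 SD, 25 per arm, two-sided 0.05, no multiplicity adjustment and a normal approximation:

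| ρ (assumed) | Level | Change | Baseline-adjusted |
|---|---|---|---|
| 0.3 | 0.81 | 0.67 | 0.84 |
| 0.5 | 0.81 | 0.81 | 0.90 |
| 0.7 | 0.81 | 0.96 | 0.98 |

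**Chance imbalance.** If the arms differ by d at baseline, the level contrast is shifted on average by ρd and the change score by −(1 − ρ)d. At ρ = 0.3 these are 0.3d and −0.7d. Only the adjusted contrast removes the shift.

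**The case against.** The strongest reply is that the sections fit together: Microarray analysis names the model, the other two name the contrast, and the time points meant are weeks 12 and 24. A repeated-measures model can deliver a change contrast, and a condensed article may leave baseline handling to the full protocol or analysis plan. The analysis is also a secondary screen, with PCR confirmation, in a self-described pilot. Much of this stands. It keeps the point small and means that no loss has been demonstrated. It does not remove the mismatch, because the article states the contrast in three places and one differs from the other two.

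A reader might infer three stronger things, none of which the document supports:

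- **That the model tests a different quantity.** Under randomisation the expected baselines are equal, so the level and change contrasts have the same expectation. The simulation shows this.
- **That the baseline array is discarded.** The text does not say so, and baseline may be one of the repeated measures. The accurate statement is that its precision is not secured.
- **That genes would be selected on pre-treatment differences, undermining the false discovery rate.** Chance imbalance is already in the standard error of the level contrast, so the error control holds.

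Nor would switching to a plain change score be a clear gain. At ρ = 0.3 it is less precise than the level contrast (1.40) and is moved further by chance imbalance.

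**Conclusion.** The inconsistency is real and minor. Microarray analysis specifies an arm comparison at each visit, whereas the endpoint definition and the profiling section specify the arm difference in change at weeks 12 and 24. Both aim at the same treatment effect, but they are different estimators and can select different genes.

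The precision left unsecured depends on a correlation that the document does not give. Against a baseline-adjusted contrast, the variance saving is 9% at ρ = 0.3, 25% at 0.5, 49% at 0.7 and 64% at 0.8. These figures assume equal variances, complete data and large-sample formulas; with 25 per arm, estimating the adjustment costs a little.

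The equality of targets assumes that those who remain are still comparable across arms. The plan allows for 50 completers out of 70 and removes participants for events it attributes to spironolactone, such as hyperkalemia. If losses differ by arm, using each patient's baseline would reduce that exposure, which is a further reason to put it in the model.

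**What to change.** Reword the model sentence in Microarray analysis so that, for each gene, the linear mixed model tests the arm difference at week 12 and at week 24 with the baseline array in the model, either with arm means constrained equal at baseline or with baseline expression as a covariate. State that the false discovery rate applies to those contrasts.

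This also reconciles the three sections. With a common baseline mean, the arm difference at a visit and the arm difference in change to that visit are the same parameter. With baseline as a covariate, the arm effect is the same whether level or change is the outcome. An unadjusted change score should not be used in its place.

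The cost is one sentence, fixed before unblinding. The baseline arrays are already planned, so no new samples or assays are needed.
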